### Patient retention

Patient retention is promoted in several ways. When participating in the specific rehabilitation programme, the patient is in regular contact with the Radboudumc treatment team (i.e. first five weekly visits, followed by two biweekly visits and two monthly visits over a 17-week period). Patients in the usual care group will be contacted at least twice during the 17-week control treatment period. The coordinating researcher will contact them by phone to inquire how the patient is and to remind them of the dairy in which they keep track of the care and/or treatment they have received. Both groups will be reminded about the post-treatment measurement(s) in the week prior to the upcoming visit.

### Intervention

The intervention under investigation is the rehabilitation programme developed and offered at the Radboudumc. This experimental intervention is compared to the usual care for NA in the Netherlands.

#### Experimental intervention

The experimental intervention is a 17-week specific rehabilitation programme. The programme starts with a visit to the specialised outpatient ‘Plexus clinic’ in week 1. During this visit, the patient is examined by a multidisciplinary team consisting of a rehabilitation physician, neurologist, physical therapist and occupational therapist. This specialised multidisciplinary team analyses the problems of the patient and provides a diagnosis and treatment advice. This treatment advice is implemented through four weekly sessions in weeks 2–5, two biweekly sessions in weeks 6–9 and two monthly sessions in weeks 10–17 (see Fig. 4 for an overview). Each of the eight treatment sessions involves one hour of occupational therapy and one hour of physical therapy. When needed, interdisciplinary strategies are employed.

**Fig. 4 Fig4:**
[figure not shown]
Overview of assessments and treatment for the intervention group (**a**) and the usual care group (**b**). A single treatment session consists of 1 h of physical therapy and 1 h of occupational therapy. BM, baseline measurement; PP, visit to out-patient plexus clinic; TS, treatment session; OM, outcome measurement; F-U, follow up

The model depicted in Fig. 5 forms the basis for the rehabilitation programme. This model consists of several components that are addressed during the intervention programme. The programme combines strategies of relearning motor control to normalise scapular stability and coordination [39], with strategies focused on self-management, including energy conservation [40], to enable daily occupations. The focus and extent to which components are addressed are adjusted to accommodate individual patients’ needs. For a full description of the rehabilitation programme, see IJspeert, Janssen [14] and van Eijk, Groothuis [7].

**Fig. 5 Fig5:**
[figure not shown]
Treatment model with the components addressed during the rehabilitation programme. Issues in the outer two circles (External factors, Activity and Participation) form the main focus of the occupational therapy sessions. During the physical therapy sessions, the main focus is on improving body functions. All other components (i.e. disease knowledge, fatigue, pain, behaviour and self-efficacy and self-management) are addressed during occupational and physical therapy. This is accomplished through conveying knowledge of neuralgic amyotrophy and adaptation of behaviour related to functioning in daily life. Reproduced with permission from IJspeert et al. NeuroRehabilitation 2013;33:657–665 [14]

#### Usual care (control group)

The 25 patients with NA in the control group will receive usual care for 17 weeks. The usual care may vary for each individual, and may even consist of no treatment at all. Patients are asked to keep a diary during this period, in which they will report on the care/treatment they receive, including the type of care (e.g. physical or occupational therapy, acupuncture), number of sessions and composition of the care (e.g. strength training, aerobic training, massage). After 17 weeks, patients in the usual care group will start with the 17-week rehabilitation programme at the Radboudumc as described above.

#### Co-interventions

During the experimental intervention, co-interventions can be employed if needed. These co-interventions may include but are not limited to analgesics and steroid medication. While undergoing the experimental intervention, patients are asked to refrain from seeking additional treatment for the upper extremity outside the scope of the rehabilitation programme (e.g. additional therapy or care), unless this is discussed with the treating physician in advance. The use of any co-interventions will be registered.

Study participants are not allowed to participate in any other scientific study that might interfere with their participation in the NA-CONTROL study (from signing informed consent to completing the follow up from home).

#### Post-trial care

If deemed necessary by the treating clinician and desired by the patient, the treatment can be extended after the nine sessions that are part of the experimental intervention.

### Data collection and management

#### Data collection

Data will be collected as described under “Outcomes”. The assessor (the coordinating researcher) conducting the measurements is trained in collecting all measures that are obtained during the measurement protocol (i.e. operating MRI systems, applying bipolar EMG surface electrodes, conducting force measurements, palpating bony landmarks of the scapula and trunk, etc.).

#### Data management system

Most data are collected through laboratory-based measurement systems, or entered directly into the electronic case report form (CRF) in a GCP-compliant electronic data management system (Castor EDC, www.castoredc.com). This system utilises a log system with an automated audit trail. The Delegation of Responsibilities Log will identify all individuals responsible for data collection and handling, and management of the database.

A data management plan, detailing location of and access to study data and the code list, method of coding, back-up, locking and archiving of data, code list and analysis files has been submitted to and approved by the Board of Directors of the Radboudumc.

### Statistics and data analysis

#### Proposed analysis

All continuous variables will be summarised as the number of (missing) observations, mean, standard deviation, median and range. Categorical variables will be summarised as the number of (missing) observations and number and percentage in each category. This will be done separately for each time point (baseline, outcome measurement(s) and follow up) and for the change from baseline for each intervention group.

The primary clinical outcome (SRQ-DLV score) and most other clinical outcomes are linear or quasi-linear. Group differences in the effects of the intervention on primary and secondary outcome measures and the influence of possible effect modifiers will be investigated using generalised estimated equations analysis. If necessary, analyses will be adjusted for group differences in functional capability of the upper extremity (SRQ-DLV score), age and sex at baseline. Data will be analysed according to the intention-to-treat principle. Data will be appropriately transformed if necessary, to satisfy modelling assumptions. Prior to locking of the data, a statistical analysis plan will be drawn up and approved by a statistician and the principal investigator.

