#### Primary outcome

##### Functional capability of the upper extremity

The primary outcome measure for the clinical part of the RCT is the change in SRQ-DLV score from baseline to post intervention. The SRQ-DLV is a reliable and validated questionnaire measuring functional capability of the shoulder, arm and hand [16] and has been shown to be sensitive to (changes in) functional capability of the shoulder in patients with NA [14].

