
#### Other parameters

Some measures will be collected to describe the study population and if applicable, to correct for possible confounding effects:A.Demographics: demographic data that will be collected includes age, sex and education levelB.NA characteristics: data on several characteristics of patients with NA will be collected. These include disease onset and duration, history of prior attacks and use of medication. Other characteristics may include, presence of atrophy, pattern of motor paresis, mechanical sensitivity of the plexus to pain, maximal severity of paresis during the attack and duration of primary pain.C.Comorbidity: relevant information on comorbid conditions and medication use will be collected.D.Motor imagery ability: there are individual differences in motor imagery ability [34]. As a subject’s ability to imagine movements might affect his/her performance on the motor imagery tasks in this study, motor imagery ability is assessed with the short version of the Kinesthetic and visual imagery questionnaire (KVIQ-10)*.* The KVIQ-10 assesses the clarity of the image (visual), and the intensity of the sensations (kinesthetic), that the subject is able to imagine from the first-person perspective [35].

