### Randomisation and blinding

Patients with NA will be randomly assigned to either the experimental intervention or to the usual care in a 1:1 ratio. Patients are randomized using a Good Clinical Practice (GCP)-compliant system (Castor Electronic Data Capture), which employs stratified, variable block randomisation. To prevent uneven distribution of certain characteristics across groups, randomisation will be stratified according to two factors: sex (male/female) and age (4 blocks: 18–30, 30–42, 42–54, > 54 years). Randomisation will be performed on site (at the Donders Institute for Brain Cognition and Behaviour, Centre for Cognitive Neuroimaging) after the participant has completed the baseline measurement (see Table 1).

Due to the project design, it is not possible to blind participants or the assessor. Participants will inevitably know whether they are receiving the rehabilitation programme or usual care. The assessor cannot be blinded either, for multiple reasons: all assessments are performed by a single assessor; as the number of assessments differs across groups, the assessor will know which participant belongs to which group; as the rehabilitation programme takes place at the assessor’s workplace facility, the assessor could be un-blinded on encountering a participant visiting the facility for treatment.

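### Adjustment of the primary analysis for baseline SRQ-DLV, age and sex should be fixed in advance, not made conditional on observed baseline differences

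*Protocol article*

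**What the plan says.** The primary outcome is "the change in SRQ-DLV score from baseline to post intervention" (Primary outcome section). Under Proposed analysis, group differences "will be investigated using generalised estimated equations analysis"; how the baseline value enters that model is not stated. The covariate rule follows: "If necessary, analyses will be adjusted for group differences in functional capability of the upper extremity (SRQ-DLV score), age and sex at baseline". No test, threshold or other criterion defines when adjustment is necessary.

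Under Randomisation and blinding, "randomisation will be stratified according to two factors: sex (male/female) and age", the latter in four bands, which makes 2 × 4 = 8 strata with 1:1 allocation. The same section says that "it is not possible to blind participants or the assessor".

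On timing, Proposed analysis says: "Prior to locking of the data, a statistical analysis plan will be drawn up and approved by a statistician and the principal investigator". The sample size section gives 42 patients as required and 50 to be included.

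**The concern.** The sentence states a rule, and the rule has the wrong trigger. After proper randomisation, any baseline difference is due to chance, so its size does not show whether a covariate is worth including. What matters is whether the covariate predicts the outcome or was used to stratify. Baseline SRQ-DLV can be expected to predict later SRQ-DLV. Sex and age define the strata.

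The rule also works against the design. Stratifying by sex and age is meant to prevent imbalance in exactly those factors, so a rule that waits for imbalance would rarely bring them in.

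Two things are at stake. One is precision, in a trial planned on 42 evaluable patients. The other is that, with no criterion, two primary models remain available until someone chooses between them.

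**Working it through.** The document attaches no figure to the adjustment, so there is none to reproduce on this point. The 42 patients serve only as a scale; how 42 was derived is a separate question.

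**Inputs from the document:** conditional rule without criterion; change in SRQ-DLV as outcome; 8 strata; 1:1 allocation; 42 evaluable patients.

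**Assumed inputs:** baseline to follow-up correlation r of 0.3, 0.5 or 0.7; equal variance σ² at both visits; age and sex explaining 0, 10 or 20% of the variance of the change; a trigger of p < 0.05 for a baseline difference; ordinary least squares at one post-baseline visit standing in for the GEE.

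**Step 1: precision from baseline SRQ-DLV.** The variance per patient is 2σ²(1 − r) for an unadjusted change score and σ²(1 − r²) after adjustment for baseline. The ratio is (1 − r²) / [2(1 − r)] = (1 + r)/2. If the change-score test had 90% power, the adjusted test would have power Φ[(1.960 + 1.282)/√ratio − 1.960]. For r = 0.5 this is 3.242/0.866 − 1.960 = 1.783, or 96%.

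| r | Variance ratio | Patients giving the precision of 42 unadjusted | Power if the change score has 90% |
|---|---|---|---|
| 0.3 | 0.65 | 42 × 0.65 = 27.3, so 28 | 98% |
| 0.5 | 0.75 | 42 × 0.75 = 31.5, so 32 | 96% |
| 0.7 | 0.85 | 42 × 0.85 = 35.7, so 36 | 94% |

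**Step 2: would an imbalance rule bring the covariates in?** Trials of 42 patients were simulated with 8 strata and permuted blocks of 2 or 4 (4000 null and 2500 alternative runs per setting). The assumed trigger fired in about 5% of trials, as chance predicts. It fired on SRQ-DLV every time, and on age or sex in 0.0% of trials.

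**Step 3: what each strategy does.** Ranges are over all settings of r and of the age and sex effect, with the true effect sized so that the unadjusted test had 85–90% power.

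| Strategy | Type I error | Power |
|---|---|---|
| Unadjusted change score | 0.034–0.054 | 85–90% |
| Adjust only if baseline p < 0.05 | 0.029–0.048 | 85–90% |
| Always adjust for baseline, age and sex | 0.044–0.055 | 92–98% |
| Report the better of the two p-values | 0.058–0.080 | not a valid test |

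**Step 4: direction of the standard-error effect.** When age and sex explained 10–20% of the variance of the change and were left out, the unadjusted test had type I error of 0.034–0.048. At r = 0.5 and 20%, the mean estimated standard error was 0.337 against a true standard deviation of the estimate of 0.308. The test was therefore conservative.

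**The case against.** **The article names the stratification factors.** A reader might infer that the analysis ignores the stratified randomisation. It does not: the sentence lists both sex and age as covariates. What is missing is a guarantee that they enter.

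**No threshold is stated.** The p < 0.05 trigger is an assumption. A looser reading of when adjustment is necessary would lead to adjustment more often and shrink the loss. This stands, and it limits Steps 2 and 3 to an illustration of one plausible rule.

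**Type I error is not inflated by the rule itself.** A reader might infer that the stated rule breaks the 5% level. The simulations do not show that. The 6–8% needs someone to fit both models and keep the better one, which the document does not describe. The article promises an analysis plan approved by a statistician before data lock, and it does not say that the statistician is unblinded. Even so, approval before lock in an open-label trial does not ensure that the model is fixed before outcomes by group are seen.

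**The GEE may already use baseline well.** If baseline is modelled as a response with a common mean in both groups, much of the gain is already there. If baseline means are left free by group, the complete-data contrast is the change-score difference and the gain is lost. The article does not say which applies, so the figures in Step 1 are upper values for the stated r.

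**Covariate detail is normally left to the analysis plan.** True of detail. Here, though, the article sets a principle, adjustment triggered by observed differences, and that principle should be replaced.

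**Conclusion.** The point holds as a matter of efficiency and prespecification. The protocol ties adjustment to observed baseline differences, without a criterion, when prognostic value and stratification should decide it.

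Against an unadjusted change score, always adjusting for baseline SRQ-DLV reduces the variance to 65–85% for an assumed r of 0.3 to 0.7, and by less if the GEE already uses baseline efficiently. Omitting sex and age costs further power only if they are prognostic, which the document does not establish; the resulting error is conservative. A claim that the planned analysis is invalid, or that its type I error is inflated as written, is not supported. The rise to about 6–8% is conditional on choosing the model after seeing results. The change is worth making, but the trial's validity does not turn on it.

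**What to change.** Replace the conditional sentence with:

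> The primary between-group comparison of SRQ-DLV at 18 weeks (equivalently, change from baseline) will always be adjusted for baseline SRQ-DLV, sex and age, within the planned GEE framework; an unadjusted analysis is a sensitivity analysis.

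The two outcome forms are equivalent because, with baseline as a covariate, the treatment coefficient is the same for the 18-week score and for the change. The sentence therefore stays consistent with the stated primary outcome.

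Apply the same rule, with each outcome's own baseline value, to secondary outcomes measured at baseline and 18 weeks in both groups. This excludes the COPM, which is taken only at the first and last rehabilitation sessions as a within-patient comparison. Fix the model in the analysis plan before any outcome data are seen by group.

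Disease characteristics are also collected ("These include disease onset and duration, history of prior attacks and use of medication"). Adding one of them, such as time since onset, is optional and would need the same advance commitment.

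Cost: one sentence and no new data. With age continuous the model spends 1 + 1 + 1 = 3 degrees of freedom. Four age bands would make it 1 + 1 + 3 = 5, and dummies for all 8 strata plus baseline 7 + 1 = 8, which is less attractive with about 42 patients.

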#### Number of participants and sample size calculation

In total, 50 patients with NA will be recruited for participation in this study. The required sample size was calculated from the results from the pilot study on the effect of the rehabilitation programme [14]. The improvement in functional capability of the upper extremity measured with the Shoulder Rating Questionnaire, Dutch Language Version (SRQ-DLV) was used for this sample size calculation. With a conservative standardised effect size of 0.29 (improvement in SRQ-DLV [14]), power of 0.90 and two-tailed testing (α = 0.05), we calculated a required sample size of 42 patients. Assuming 20% dropout or non-compliance, we need to include 50 patients with NA.

The Radboudumc hosts the national referral centre and the only expert multidisciplinary outpatient clinic for patients with NA in the Netherlands. Each year around 400 new patients with NA are seen, most referred by Dutch neurologists or general physicians. Of these 400 patients, about 40% are estimated to be eligible for inclusion (see “Inclusion criteria”). We therefore expect to be able to recruit sufficient patients with NA for this study within the 2-year inclusion period.

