#### Missing data

Throughout data collection, measures will be taken where possible to minimise the occurrence of missing data. These measures include those mentioned under “Patient retention” and clear communication with individuals involved in data collection.

Once data collection is complete, the extent of missing data will be evaluated. Any patterns in missing data will be explored, especially in relation to the intervention groups. Missing data will be imputed if necessary and if possible.

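### In an open-label trial, data lock is too late as the only deadline for the analysis plan, and adjustment of the primary comparison should not depend on observed group differences

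*Protocol article*

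**What the plan says.** On timing, *Proposed analysis* in the protocol article states: "Prior to locking of the data, a statistical analysis plan will be drawn up and approved by a statistician and the principal investigator". No earlier milestone is given.

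The same section names generalised estimating equations and the intention-to-treat principle. It lists baseline SRQ-DLV, age and sex as the covariates, but brings them in only where differences between the groups make it necessary. It does not say what counts as necessary. Two further choices are conditional: "Data will be appropriately transformed if necessary, to satisfy modelling assumptions" and, under *Missing data*, "Missing data will be imputed if necessary and if possible". The latter follows an inspection of missingness patterns by arm once collection is complete.

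On blinding, *Randomisation and blinding* says that "it is not possible to blind participants or the assessor". One assessor makes all assessments, and *Data collection* identifies that person as the coordinating researcher. Randomisation is stratified by sex and age.

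**The concern.** Finishing the SAP before lock protects a blinded trial because outcomes cannot be split by arm until the code is broken. Here allocation is known throughout, so lock is not the first moment at which SRQ-DLV scores could be compared by arm. A SAP that meets the stated deadline could still be written after that comparison was possible.

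The adjustment rule adds to this. With no stated trigger, whether to adjust stays a matter of judgement. The rule is also weak in itself: sex and age were stratified on, and baseline SRQ-DLV is the natural covariate for a change in SRQ-DLV, so all three belong in the model whatever imbalance is seen. At stake is how readily a positive result can be defended, on a self-reported outcome in 50 unblinded patients.

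**Working it through.** **Inputs from the article.** The test level comes from the sample size section: "power of 0.90 and two-tailed testing (α = 0.05), we calculated a required sample size of 42 patients". Fifty patients are randomised 1:1, so 25 per arm. The primary outcome is the change in SRQ-DLV, compared between arms at 18 weeks.

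**Inputs assumed, not in the article.** Baseline to follow-up correlation ρ of 0.3 to 0.85; 16% missing; SRQ-DLV mean 60, SD 15, range 17 to 100; a log as the transformation; last value carried forward as the imputation. Ordinary least squares at one follow-up visit stands in for generalised estimating equations.

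**Step 1: the time window.** The between-arm comparison is complete at 18 weeks, but usual-care patients are followed to 54 weeks. If lock follows the last follow-up (an assumption), the window for the last patient is 54 − 18 = 36 weeks. Recruitment began in March 2018, so 18-week scores accrue from about July 2018, and the window is longer for earlier patients.

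**Step 2: the nominal level.** A single analysis fixed in advance should return 0.05. Simulated under no effect (6,000 trials per setting), it gives 0.048 to 0.052.

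**Step 3: free selection.** The trial is called positive if the smallest p-value over the open analyses is below 0.05. For two analyses the rate must lie between 0.05 (identical tests) and 1 − 0.95² = 0.0975 (independent tests). Results:

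| Choices open | Analyses | ρ = 0.3 | 0.5 | 0.7 | 0.85 |
|---|---|---|---|---|---|
| None (change score) | 1 | 0.050 | 0.051 | 0.048 | 0.049 |
| None (baseline-adjusted) | 1 | 0.052 | 0.051 | 0.049 | 0.048 |
| Adjustment yes/no | 2 | 0.080 | 0.078 | 0.069 | 0.066 |
| Adjustment and transformation | 4 | 0.091 | 0.089 | 0.081 | 0.080 |
| Adjustment and imputation | 4 | 0.090 | 0.085 | 0.075 | 0.073 |
| All three, yes/no | 8 | 0.103 | 0.098 | 0.088 | 0.088 |
| Four covariate sets, transformation, imputation | 16 | 0.120 | 0.113 | 0.101 | 0.099 |

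The Monte Carlo standard error, √(p(1 − p)/6000), is 0.003 to 0.004. With 42 patients, none missing and ρ = 0.5, the adjustment choice alone gives 0.075 and the full set 0.100.

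Relative to 0.05, adjustment alone gives 0.066/0.05 = 1.3 to 0.080/0.05 = 1.6 times nominal. All three choices as yes/no give 0.088/0.05 = 1.8 to 0.103/0.05 = 2.1 times. The article names its three covariates together, so the yes/no rows are closer to its text than the 16-analysis row.

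**Step 4: a conditional rule fixed in advance.** Suppose the change score is adjusted for baseline only if the baseline test gives p below 0.05, 0.10 or 0.20 (8,000 trials each, ρ = 0.3, 0.5, 0.7, 25 per arm, none missing). Type I error is 0.032 to 0.051. There is no inflation, and in most settings the test is conservative.

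**Step 5: what unconditional adjustment gains.** With equal variance σ² at both visits, the change score has variance 2σ²(1 − ρ), and the baseline-adjusted score has residual variance σ²(1 − ρ²). The ratio is (1 − ρ²)/(2(1 − ρ)) = (1 + ρ)/2: 0.65, 0.75, 0.85 and 0.925 at ρ = 0.3, 0.5, 0.7 and 0.85. Adjustment therefore lowers the variance at every ρ below 1, whether or not the arms look unbalanced. This ignores the few degrees of freedom spent.

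**The case against.** Approval of a SAP before lock, by a statistician and the principal investigator, is a common and real safeguard. Neither approver is described as the assessor or as seeing outcomes by arm. The article refers to an approved data management plan covering access to the data and the code list, an audit trail, and access limited to appropriate staff. That plan is not shown. The article also fixes the method, the analysis principle and the candidate covariates, and it ties transformation to a purpose. All of this stands.

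Three stronger readings are tempting, and the documents do not support them:

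- A reader might infer that the plan doubles the false-positive rate. That needs all three choices open, the smallest p-value picked with results by arm in view, and alternatives such as the log that the article never names.
- A reader might infer that the conditional wording is itself the cause. Step 4 shows that a conditional rule set in advance does not inflate the error.
- A reader might infer that someone will compare the arms early. The article neither says so nor rules it out. That the assessor knows allocations is stated; that anyone tabulates outcomes by allocation is not.

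The lack of rules for transformation and imputation is no defect either, since these belong in the SAP. What the objection leaves unanswered is that the only stated deadline does not exclude a by-arm view, and that adjustment waits on observed imbalance.

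**Conclusion.** The point holds in a limited form. The article states two rules that suit this design badly: a data-lock deadline in an open-label trial, and imbalance-triggered adjustment for the baseline score and the randomisation strata. Both should be changed, though neither shows that the result will be biased.

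The possible size, if the analysis were chosen freely with results by arm in view, is a type I error of about 7–8% from the adjustment choice alone and about 9–12% with transformation and imputation also open, against a nominal 5%. These are upper bounds. They rest on the assumed correlations, missingness, scale and alternative analyses, and on least squares in place of generalised estimating equations. With the analysis fixed beforehand, the excess disappears.

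**What to change.** Make two changes in *Proposed analysis*:

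1. Require the SAP to be approved and dated before anyone tabulates or compares outcome data by arm. A calendar backstop such as the last patient's 18-week visit would protect little, because nearly all primary outcomes would be in by then.
2. Replace the conditional adjustment with an unconditional one: the primary SRQ-DLV comparison at 18 weeks is adjusted for baseline SRQ-DLV, sex and age, with the unadjusted analysis kept as a labelled sensitivity analysis. This fits the stated endpoint, since with baseline in the model the 18-week score and the change from baseline give the same treatment estimate. It can be fitted with the method already named.

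Details of transformation and imputation can stay in the SAP. The cost is small: a document already planned is brought forward, and the primary model can no longer be tailored to the observed data.
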